## 2. Methods

### 2.1. Study Objectives

The purpose of this study is to assess the feasibility of RCTs on clinical effectiveness and safety of the four-week Korean integrative treatment program for severe spinal stenosis, comparing different types of Mokhuri treatment programs and the usual care in conventional medicine in inpatient units. Information related to the compliance of the study design and interventions, the implementation of outcome assessments, and the sample size calculation for the full sized RCTs will be analyzed in this study. The null hypothesis of the primary outcome is that the change of 0-to-100 visual analogue scale (VAS) for low back pain and leg pain before and after treatment will be the same in the following three patient groups: Mokhuri treatment program group 1 (MT1 group) that will be treated with herbal medication, Chuna, acupuncture, and patient education; Mokhuri treatment program group 2 (MT2 group) that will be treated with Chuna, acupuncture, and patient education; or the usual care group that will be treated with analgesics, epidural steroid injection, and physiotherapy.

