### 2.2. Methods

This study is a corporative clinical study with Spine Center of Mokhuri Oriental Medical Hospital, Korea Institute of Oriental Medicine, and Complementary and Integrative Medicine Program of Mayo Clinic. The study design was developed through discussion among the three organizations, and the clinical study will be conducted in Mokhuri Hospital. The study protocol was approved by the Institutional Review Board of Mokhuri Hospital (MHNBH-14001). A total of 36 LSS patients with intractable symptoms that did not subside by at least three months of conventional treatment will be recruited through advertisements in newspapers and websites for these patient communities. This is a pilot study for future, full-scaled clinical trials. As a result, 12 patients will be recruited for each group without a sample size calculation for the minimum participant number according to statistical analysis of their basic information, considering possible dropouts. Because patients with both spinal stenosis and spondylolisthesis and therapeutic responses of spinal stenosis with and without spondylolisthesis are expected to differ, we will recruit 2 patients with spondylolisthesis into the 12 participants of each group to assess the difference in the clinical outcomes. The study will be conducted at the Spine Center of Mokhuri Hospital, Seoul, South Korea. In the clinical research information service (CRIS, a representative clinical trials registry platform in Korea), the protocol was registered before the first participant is included (registration number: KCT0001218). Any patients who meet the inclusion criteria and provide written informed consent for participation in the study will be randomly allocated into one of three groups, the MT 1, MT 2, or usual care groups. For sequence generation, stratified random numbers for whether the patients do or do not have spondylolisthesis will be generated using the SAS 9.2 package software. Opaque sealed envelopes will be used to conceal which group patients have been allocated to. Over a period of four weeks, each treatment will be offered in the inpatients unit. Patients will be urged to visit the research center for follow-up evaluation at three and six months after the four weeks of treatments.

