### 2.8. Statistical Analysis

Statistical analysis will be conducted on the basis of intention-to-treat analysis (ITT). Missing values will be imputed by the last observation carried forward (LOCF) method. Baseline characteristics will be presented as the mean and standard deviation (SD) for continuous outcomes and as the frequency for categorical outcomes. Statistical analysis between groups will be conducted with a *t*-test (Wilcoxon rank sum test in case of nonnormal distribution data) or a chi-square test, respectively. Primary and secondary outcomes will be analyzed with analysis of covariance (ANCOVA), with the change in the outcome scores between the groups as the dependent variable, baseline scores as a covariate, and study groups as a fixed factor. Pre- and posttreatment differences in each group will be analyzed with a *t*-test (Wilcoxon rank sum test) or a chi-square test. Repeated measures analysis of variance will be conducted to identify the trend in data. The frequency of AEs in each group will be compared using Fisher's exact test. The types of AEs will be assessed through qualitative analysis.

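### Section 2.8 names independent-sample tests (rank sum, chi-square) for pre/post change within each arm, although the same patients are measured twice

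*Protocol article*

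**What the plan says.** Section 2.8 of the protocol article sets out three comparisons that matter here.

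- **Baseline and groups.** The text first says "Baseline characteristics will be presented as the mean and standard deviation (SD) for continuous outcomes and as the frequency for categorical outcomes". The next sentence reads "Statistical analysis between groups will be conducted with a *t*-test (Wilcoxon rank sum test in case of nonnormal distribution data", adds a chi-square test, and closes by matching the tests to the two kinds of variable just named.
- **Outcomes between arms.** "Primary and secondary outcomes will be analyzed with analysis of covariance (ANCOVA", with "baseline scores as a covariate, and study groups as a fixed factor".
- **Change within each arm.** "Pre- and posttreatment differences in each group will be analyzed with a *t*-test (Wilcoxon rank sum test) or a chi-square test".

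No paired test is named anywhere in the article. Section 2.2 says that patients will be "randomly allocated into one of three groups, the MT 1, MT 2, or usual care groups" and that "12 patients will be recruited for each group without a sample size calculation". Section 2.1 states the primary null hypothesis for all three arms together: change in VAS "will be the same in the following three patient groups". Section 2.6 has every outcome measured both before and after treatment, so the within-arm data are paired.

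**The concern.** Both the rank sum test and the ordinary chi-square test treat their two samples as different people. Within an arm, the pre and post samples are the same 12 patients. The rank sum test then discards the pairing, and the chi-square test counts each patient twice, as if 24 people had been observed. The tests that use the pairing are the Wilcoxon signed-rank test and, for categories, McNemar's test or its extension by Bowker. The sentence on group comparisons names the same three tests, so the text does not separate paired from independent data.

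At stake are the reported within-arm p-values. The rank sum test would be a natural choice with 12 patients per arm and bounded scales, and it could miss a change that the correct test would show. The Discussion says the findings will serve as basic data for a full-scale trial, so the wording could carry over.

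The lesser issue is that a t-test or rank sum test compares two groups, so neither can compare three arms in one step.

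**Working it through.** **Inputs from the protocol article:** 12 patients per arm and three arms (section 2.2); the same patients measured before and after (section 2.6); the tests named in section 2.8.

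**Assumptions, because the article gives no figure:** two-sided 5% level, normal data with equal SD before and after, pre/post correlation ρ from 0 to 0.7, and a shift of 0 to 1.0 SD. There is no power or error figure in the plan to reproduce.

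**Why pairing matters.** With n pairs and SD σ, the variance of the mean change is 2σ²(1−ρ)/n. A test that assumes independence behaves as if it were 2σ²/n. The standard error is therefore too large by a factor of 1/√(1−ρ):

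- ρ = 0: 1/√1 = 1.00
- ρ = 0.3: 1/√0.7 = 1.20
- ρ = 0.5: 1/√0.5 = 1.41
- ρ = 0.7: 1/√0.3 = 1.83

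This formula is for means, but the rank sum test behaves in much the same way, as the simulation shows.

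**Simulation, n = 12, 20,000 runs per setting.** Proportion of runs rejecting at 5%:

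| ρ | No change: rank sum | No change: signed-rank | 0.8 SD: rank sum | 0.8 SD: signed-rank | Signed-rank minus rank sum |
|---|---|---|---|---|---|
| 0 | 0.044 | 0.042 | 0.431 | 0.392 | −0.039 |
| 0.3 | 0.020 | 0.042 | 0.417 | 0.520 | 0.103 |
| 0.5 | 0.008 | 0.041 | 0.414 | 0.669 | 0.255 |
| 0.7 | 0.002 | 0.041 | 0.412 | 0.868 | 0.456 |

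Other shifts give the same picture. At ρ = 0.5, rank sum against signed-rank is 0.132 against 0.313 for 0.5 SD, and 0.646 against 0.853 for 1.0 SD.

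With positive correlation the rank sum test therefore rejects too rarely when nothing has changed and loses power when something has. At ρ = 0 it loses nothing. The chi-square test was not simulated; the objection to it is the double counting described above.

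**Three arms.** In the planned ANCOVA, group has three levels, so its test has 2 and 36 − 4 = 32 degrees of freedom. Simulated with no true difference between arms (20,000 runs), it rejects in 0.0496 of runs. The three-group null in section 2.1 is thus tested at the nominal level by the analysis planned for the outcomes.

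**The case against.** **The t-test can be read as paired.** Section 2.8 applies it to differences within each group and does not call it unpaired. Leaving out the word paired is ordinary shortening in an article. This stands, so the firm error is confined to the rank sum and chi-square tests.

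**No inflated error for the outcomes.** A reader might infer that two-sample tests in a three-arm trial mean several unadjusted pairwise tests of the primary VAS scores, with more false positives. The document does not support this. The sentence follows the one on baseline characteristics and matches its tests to the continuous and categorical variables named there, so it most naturally concerns baseline comparability. The next sentence assigns the outcomes to ANCOVA. The article states no pairwise scheme and no significance level, and the chi-square test can take three groups. What remains is that the two tests for continuous variables do not fit three arms.

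**The loss is conditional and was computed on normal data.** It depends on an assumed correlation: about 10 points at 0.3 and none at 0. The rank sum test is meant for nonnormal data, so the simulated figures illustrate the loss and do not predict it. This also stands. It limits how precise the size can be; it does not make the test suitable for paired data.

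**Little depends on these tests.** They are supplementary, the error is conservative under positive correlation, and this is a 36-patient feasibility pilot. That is a fair argument about severity.

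**Conclusion.** The naming error is real and minor. Section 2.8 prescribes the rank sum and chi-square tests for data on the same patients measured twice, and following it as written gives wrong within-arm p-values. With n = 12, normal data, a two-sided 5% level and a 0.8 SD shift, the power lost against signed-rank is about 10, 26 and 46 percentage points at correlations of 0.3, 0.5 and 0.7, and none at 0. The correlations, the shift and the level are all assumptions.

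Secondarily, the t-test and rank sum test named for comparing groups cannot handle three arms at once. This bears on the baseline table. The ANCOVA of the primary and secondary outcomes and the feasibility measures are unaffected.

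**What to change.** In section 2.8:

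- For change within an arm, name the paired t-test, the Wilcoxon signed-rank test for nonnormal data, and McNemar's test for two categories or Bowker's for more. Label these results descriptive.
- For continuous baseline variables across the three arms, name one-way ANOVA or Kruskal-Wallis, or tabulate them without a test. The chi-square test can stay for categorical baseline variables.

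The ANCOVA needs no change on this account. The cost is a few words in the text, with no extra patients, visits or data.

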### 2.3. Inclusion Criteria

Patients who are aged 19 to 77 years with clinical symptoms and signs consistent with LSS, including low back pain, radicular leg pain, or leg discomfort when standing or walking, will be included in the study. The patients should have experienced claudication or radicular leg symptoms for at least one year and lack symptomatic relief from pain; also, function related to LSS should be experienced after at least three months of sufficient conservative nonsurgical treatments, including epidural injection therapy, administration of analgesics, and (or) physiotherapies. He or she needs to be diagnosed with LSS through CT or MRI and have been recommended for decompression and (or, additionally) fusion surgery by neurosurgeons or orthopedic doctors. Neurogenic claudication should appear within five minutes of walking on a treadmill with a speed of at least 1.5 miles/hour. Finally, the patient should not have been treated with an epidural injection during the last 1 month.

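### Within-arm before/after significance tests beside the ANCOVA do not address the between-arm hypothesis, invite misleading reporting, and name an unpaired test for paired data

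*Protocol article*

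**What the plan says.** Section 2.1 states the primary null hypothesis as a comparison between arms: the change in the 0-to-100 VAS for back and leg pain "before and after treatment will be the same in the following three patient groups".

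Section 2.8 sets an analysis that fits it: "Primary and secondary outcomes will be analyzed with analysis of covariance (ANCOVA"), with change as the dependent variable, baseline score as covariate and study group as fixed factor. The same paragraph then adds a second layer: "Pre- and posttreatment differences in each group will be analyzed with a" t-test, with the Wilcoxon rank sum test in brackets, or a chi-square test. It gives this layer no purpose, does not call it descriptive and sets no limit on its interpretation.

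Four design features bear on how a within-arm change can be read:

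- **Arm size.** Section 2.2: "12 patients will be recruited for each group without a sample size calculation".
- **Setting.** All three arms are treated for four weeks in the inpatient unit (Sections 2.2 and 2.5), and each receives active treatment.
- **Entry.** Section 2.3 asks for a lack of relief, in that "function related to LSS should be experienced after at least three months of sufficient conservative nonsurgical treatments", and for a surgical recommendation. It also sets a measured cut-off: "Neurogenic claudication should appear within five minutes of walking on a treadmill".
- **Outcomes.** Section 2.6 makes the two VAS scores primary and includes treadmill and walking tests among the secondary outcomes.

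**The concern.** A before/after test in one arm asks whether that arm's mean changed. It does not ask whether the arms changed by different amounts, which is the stated hypothesis. With no untreated arm, a fall in pain or a gain in walking within an arm may reflect treatment, natural course, or four weeks in hospital. For outcomes tied to the treadmill entry criterion it may also reflect regression to the mean. The within-arm p-value cannot tell these apart.

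The second problem is comparison by eye. With three p-values side by side, a significant result in one arm and a non-significant one in another is easily read as a difference between programmes. At 12 patients per arm that pattern can arise often when the arms do not differ at all.

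The third is a plain error in the same sentence. Scores before and after treatment come from the same patients, but the Wilcoxon rank sum test is for two independent samples.

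**Working it through.** **Inputs from the protocol.** Three arms, 12 patients per arm (Section 2.2). The plan states no alpha, SD, effect size or power for these tests, so it has no figure to reproduce.

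**Assumptions.** Two-sided 5% level; paired t-test with 12 − 1 = 11 degrees of freedom; SD of the change score 20 points; the same true fall in every arm, so no between-arm effect; one outcome; independent arms.

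**Formulas.** For a shared fall *d*, the noncentrality is (*d*/20) × √12. The noncentral t distribution then gives *p*, the chance that one arm is significant.

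- At least one of three arms significant: 1 − (1 − *p*)³
- Arms disagree (some significant, some not): 1 − *p*³ − (1 − *p*)³

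Example at 10 points: noncentrality 0.5 × 3.464 = 1.732 and *p* = 0.353. At least one arm: 1 − 0.647³ = 0.729. Disagreement: 1 − 0.353³ − 0.647³ = 0.685.

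| Shared fall (points) | One arm significant | At least one of three | Arms disagree |
|---|---|---|---|
| 0 | 5.0% | 14.3% | 14.3% |
| 5 | 12.4% | 32.9% | 32.7% |
| 10 | 35.3% | 72.9% | 68.5% |
| 12 | 47.5% | 85.5% | 74.8% |
| 15 | 65.8% | 96.0% | 67.5% |
| 20 | 88.3% | 99.8% | 31.0% |
| 25 | 97.6% | >99.9% | 7.2% |

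**Dependence on the SD.** Only the ratio of fall to SD matters. With an SD of 15, disagreement is 31% at a 15-point fall and 4% at 20.

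**The planned ANCOVA under the same conditions.** A simulation of 6,000 trials per setting (correlation 0.5 between before and after scores) gave a false-positive rate for the three-group test of 4.2% to 5.1% for shared falls from 0 to 1.0 SD. This is expected, because a constant added to every patient's change leaves the group comparison untouched.

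**The rank sum test on paired data.** Simulation with 12 patients, 3,000 samples per setting, correlation 0.5:

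- No change: rank sum rejects in 1.1%, signed-rank in 4.6%.
- Change of 0.5 SD of the change score: rank sum 13%, signed-rank 30%.
- The same change at correlation 0.3: 23% against 32%. At correlation 0.7: 6% against 32%.

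The named test discards the pairing and loses power. It makes the within-arm tests more conservative but does not make them answer the between-arm question.

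**The case against.** The strongest reply is that the right analysis is already in the plan. Section 2.8 assigns primary and secondary outcomes to a baseline-adjusted between-arm ANCOVA, and Section 2.1 frames the hypothesis to match. A reader might infer that within-arm p-values will be used to claim efficacy, or compared across arms. No section says so. This stands: the harm lies in reporting and reading, and this is a feasibility pilot.

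A reader might also infer that regression to the mean will lower pain scores in every arm. The criteria do not support that as a general statement. Sections 2.3 and 2.4 set no VAS threshold, and at least one year of symptoms points to persistent disease, not a passing peak. The mechanism is direct only for the treadmill and walking outcomes. Even there, Table 1 schedules walking at screening and again at week 2, so part of the effect could have passed if week 2 serves as baseline.

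It is likewise tempting to say that baseline pain describes a week at home and the later score a week in hospital. Section 2.6 says only that pain over the last week is rated, and Table 1 places the first VAS at week 2 under the inpatient heading. The home reading is plausible if week 2 is the day of admission, but it is an inference.

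Finally, disagreement is frequent only for moderate shared changes; with a very small or a large one it is much rarer. Within-arm change also has a descriptive use: Section 2.6 plans to look at canal diameter before and after treatment. Both points are accepted. Neither gives the within-arm significance tests a role in the stated hypothesis.

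**Conclusion.** The point holds as a reporting risk plus one definite error of method. The within-arm tests do not address the hypothesis in Section 2.1, and the design offers no means of attributing a within-arm change to treatment. With equal arms, 12 per arm and an assumed SD of change of 20, the arms would disagree in significance in 14% of trials with no shared fall. The rate peaks near 75% at about 12 points and returns to 7% at 25 points, against about 5% for the ANCOVA. The SD and the size of the shared fall are assumptions, because the protocol gives neither. The figures are for a single outcome and the paired t-test.

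Naming the rank sum test for before/after data is wrong whatever those values are. The main between-arm analysis is sound and is not called into question. The change is worth making because it is cheap and removes a likely source of misreading.

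**What to change.** Delete the sentence on within-arm before/after tests from Section 2.8. In its place, state that mean change with SD, or with a 95% CI, will be reported by arm as description only. State also that every inferential statement will rest on between-arm differences from the planned ANCOVA, with 95% CI. If any before/after test is kept, make it a paired t-test or a Wilcoxon signed-rank test and label it descriptive.

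The cost is one sentence and somewhat less analysis. Nothing the pilot needs is lost: the SD of change for the future sample size calculation (Section 2.7) is still reported, and no data collection changes.

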### 2.9. Data Monitoring and Dropout Criteria

Data monitoring will be conducted regularly by researchers from the Korea Institute of Oriental Medicine for fair clinical trial. Source data from the study will be handled and analyzed by an independent statistician. Patients who want to stop participating in this study, do not complete the treatment over four visits, violate the study protocol, withdraw consent for participation, and use prohibited treatments for lumbar stenosis will be dropped out from the study.

## 3. Discussion

This is a protocol for a pilot clinical trial on integrative Korean medicinal treatment for symptomatic spinal stenosis. Considering that the aging population is expected to increase, more people will suffer from LSS in the future. Spinal fusion and decompression surgeries, which are the standard treatment for symptomatic LSS, cannot ensure a long-term effect, and adverse events related to the surgery cannot be ignored. In this sense, the currently used nonsurgical treatments need to be evaluated. The findings of this pilot study will be used for the assessment of the feasibility about the study design and compliance of the interventions and outcome assessments, which can be basic data for subsequent full-scale clinical trial on the benefits and harm of this integrative Korean medicinal treatment program for symptomatic spinal stenosis.

## Figures and Tables

**Table 1 tab1:** Schedule for outcome assessment.

Stage	Screening	Treatment period in the inpatient unit				Follow-up		
Weeks	0	2	3	4	5	6	18	30
0-to-100 visual analogue scales for low back and leg pain		◯	◯	◯	◯	◯	◯	◯
EQ-5D		◯	◯	◯	◯	◯	◯	◯
Oswestry Disability Index		◯	◯	◯	◯	◯	◯	◯
Roland-Morris Disability Questionnaire		◯				◯	◯	◯
Oxford Claudication Score		◯				◯	◯	◯
Walking duration and distance without pain	◯	◯	◯	◯	◯	◯	◯	◯
Radiologic test (L-spine X-ray of flexion and extension views and L-spine MRI)	◯					*⨀*		*⨀*
Adverse events		◯	◯	◯	◯	◯	◯	◯

◯: outcome variables that will be assessed in all participants; *⨀*: L-spine X-ray of flexion and extension views will only be assessed in the patients with spondylolisthesis.
